
#### Summary of the Results of Engaging With the Digital Health Checklist

Overall, our activities resulted in the selection of the Fitbit based in part on the ethical and data management practices that are used at Fitabase, which was the digital health technology company that ultimately operationalized many of the key elements of our overall study protocol. In addition, our team devised a robust and comprehensive set of activities that were all designed to ensure that participants engaged with sets of questions to assess potential risks of participating (which largely related to potential risks that arise if a person has health challenges that would result in increasing the likelihood of adverse events due to exercising) and also helped participants make informed decisions, including the use of a motivational interviewing–style approach to informed consent that involves asking participants to develop their own personal list of the pros and cons of both participating and not participating in the study before making a final informed consent decision. In addition, our entire algorithm development process was explicitly established to be able to align with and learn each person’s priorities, interests, and goals and, from there, align with a person’s context and needs. This was done via the mixed use of both the COT approach for creating a personalized (via system ID) and perpetually adapting (via the control algorithm) approach that is all enacted in a purely idiographic (ie, N-of-1) way. This approach reduces the risk of a systemic bias of an algorithm developed nomothetically (eg, an algorithm that was trained on persons with largely light skin creating a systematic bias that reduces confidence in the results when used with persons with darker skin) as there is no requirement for all participants to have the same computational algorithm to guide personalization or the same enactment of the control algorithm to support personalization. Moreover, we included our self-experimentation Reflect tool with the explicit goal of inviting persons to cultivate their knowledge, skills, and practices for exercising, with the ultimate judge on whether a strategy is a good one being the person themselves. Through examining the key questions and challenges of the Digital Health Checklist, the team concluded that we had produced a digital health tool that could be implemented in a way that, most critically, honors individual autonomy; leans toward beneficence in the form of aligning the success of the intervention strategies directly with the goals of the person, accounting for their personal assets and constraints; and honors justice in the form of advancing an algorithmic and self-experimentation approach that, at its core, can align with each person’s unique needs while also being automated and, thus, scalable, thus providing a pathway for advancing justice in the implementation of digital health tools.

### Eligibility Criteria

The targeted population were inactive adults interested in increasing their weekly PA. Inclusion criteria were (1) age of 25 to 80 years; (2) intention of being available for a 12-month research study; (3) willingness and ability to attend 3 measurement visits at UCSD over the 12-month RCT; (4) PA deficiency (<150 MVPA minutes per week and <75 vigorous PA minutes per week based on the International Physical Activity Questionnaire) [73]; (5) passing the conditional logic of the Physical Activity Readiness Questionnaire–Revised (PAR-Q) [74], which screens for PA readiness, OR being approved by their physician if they did not pass the PAR-Q; (6) BMI between 18 and 40 kg/m^2^; (7) willingness and ability to use a smartphone and SMS text messaging; (8) willingness and ability to use the Fitbit Versa smartwatch and app; (9) willingness and ability to walk and engage in moderate-intensity activities; and (10) ability to speak English. Exclusion criteria were (1) a mechanical medical implant, (2) enrollment or plans to enroll in a PA program during the study period, and (3) psychiatric or medical conditions that prohibited compliance with the study protocol.

### Recruitment, Enrollment, and Retention

A diverse sample of prospective participants were recruited in the San Diego region via digital advertisements, targeted social media advertisements, posting of print and digital flyers at UCSD and community centers, emails sent by community public health partners, and county-wide events via tabling. Interested individuals were directed to complete a web-based screening form through the study’s secure REDCap (Research Electronic Data Capture; Vanderbilt University) database hosted at UCSD [75] that provided further details about the study and criteria for participating. Individuals were then asked eligibility questions, including their age, BMI, and current PA behavior via the International Physical Activity Questionnaire [73], and study staff followed up accordingly.

Prospective participants who did not meet the eligibility requirements received an email notifying them and thanking them for their interest in the study. Prospective participants who met the eligibility requirements received a call from a trained research staff member notifying them that they may be eligible to participate, informing them about the study details, explaining that they may be randomized to an active control group, and confirming the information provided in the web-based screening form. Because participants engaged in a submaximal treadmill test, those eligible were also prescreened for exercise testing using the PAR-Q [74]. Those who did not pass the conditional logic of the PAR-Q were required to obtain approval from a physician before participation. In addition, prospective participants who reported ≥3 American College of Sports Medicine risk factors [76] were referred to the study physician to determine how to proceed with exercise testing. The study physician determined whether the participant could (1) take part in exercise testing as normal, (2) take part while being monitored by an electrocardiogram, or (3) take part with clearance from the participant’s physician. Once prescreening procedures, shown in Figure 6, were completed and the prospective participant was deemed eligible, they were invited to schedule a baseline measurement appointment at the EPARC at UCSD. This entire prescreening process reflected our commitment to truly informing our prospective participants of the opportunities and potential risks, with risk assessment taking place on their behalf to ensure that they had all the information they needed to decide. With this information, prospective participants were then provided with the final written informed consent document to review it and ask questions about the study; if they agreed, they signed the consent form to conclude the enrollment process. Following written consent, the baseline measurements took place.

**Figure 6 figure6:**
[figure not shown]
Pre-enrollment screening and exercise testing procedures for YourMove. ACSM: American College of Sports Medicine; APMHR: age-predicted maximal heart rate; CV: cardiovascular, MD: medical doctor; PAR-Q: Physical Activity Readiness Questionnaire.

After eligibility, consent, and BMI were confirmed and baseline measurements were completed, participants were randomized to either the YourMove intervention or the active control at a ratio of 1:1 stratified by sex. The biostatistics team generated an electronic randomization list using the latest version of the statistical software platform R (currently version 4.1.2; R Foundation for Statistical Computing [77]). The pseudorandom seed was saved so that the code could be validated and the sequence regenerated if necessary.

To meet enrollment targets and increase retention, each participant was provided with a Fitbit Versa smartwatch and gift card incentives throughout the study. At the baseline measurement visit, after enrollment and randomization, participants received a Fitbit Versa. The device is theirs to keep upon completing at least 1 month of participation in the study. To maximize the likelihood that participants will continue with follow-up measurement visits and stay in the study, US $25 and US $50 gift cards are provided at the completion of the 6- and 12-month measurement visits, respectively, for a total of US $75. Participants in both the YourMove intervention and active control groups also receive up to US $50 over the 12-month study contingent upon meeting their assigned step goals and based on the number of points assigned to them each day. For the YourMove intervention, goals and points are assigned based on, first, the system ID experiment (to generate a personalized computational model) and then on the control algorithm to support perpetual adaptation (which, overall, we refer to as the “COT approach,” a term that we will use when referencing the overall approach regardless of phase). Daily step goals for each participant are estimated to be challenging for the person but also possible based on their step data history and predictions from the COT approach. In addition, daily points are assigned by the COT approach, with the phase 2 control algorithm set to lean toward providing the fewest number of points needed to facilitate a person meeting their step goals on any given day. For the active control, daily step goals are 10,000 steps per day. Points remain static at 150 points per day. For both groups, 1000 points equal US $1, and the maximum amount that each participant can earn over the course of the 12-month study is US $50. The minimum monetary compensation that a participant can receive for completing the study (both in the intervention and control conditions) is US $75 by completing only the measurement visits, and the maximum monetary compensation is US $125 by achieving the maximum of US $50 for reaching the daily step goals and US $75 for completing each measurement visit.

### Measurement Protocol

#### Overview

Outcomes are measured at baseline and the 6- and 12-month follow-up. The primary outcome measure, minutes per week of MVPA, is assessed via the ActiGraph GT3x+ [49-51] using standardized procedures [50,53]. Participants are instructed to wear the device continuously during their waking hours for 7 days except while bathing or swimming. Minute-by-minute estimates of activity are categorized into intensity-weighted summaries (ie, sedentary, light, moderate, and vigorous) of PA using previously validated calibration thresholds as well as cutoff points used in national surveillance systems [49,50]. Steps per day are also determined using a proprietary algorithm from ActiGraph that has been independently validated [51].

Secondary outcome measures include anthropometric and physiological measures, behavioral measures, psychological measures, related lifestyle factors, and overall participant experience and satisfaction. Anthropometric and physiological outcomes are measured using the following standardized procedures and conducted by trained staff: (1) body weight is measured to the nearest 0.1 kg using a calibrated digital scale; (2) height is measured to the nearest 0.1 cm using a stadiometer; (3) BMI is calculated from the height and weight measurements as kg/m^2^; (4) waist and hip circumference is measured to the nearest 0.1 cm using stretch-resistant measuring tape; (5) body composition is measured through bioelectrical impedance analysis using a Tanita DC-430U dual-frequency total body composition analyzer; (6) grip strength is measured to the nearest 1 kg using a grip strength dynamometer (JAMAR; model 081669928); (7) flexibility is measured using a sit-and-reach box; (8) gait speed is measured using a 25-foot walk test; (9) the Short Physical Performance Battery and Timed Up and Go test will be conducted in participants aged ≥50 years to assess lower extremity strength, transitional movements, balance, fall risk, and mobility; and (10) the submaximal graded exercise test is conducted on a treadmill using a walking protocol.

Behavioral measures include the Global Physical Activity Questionnaire; Physical Activity Neighborhood Environment Scale; Sedentary Behavior Questionnaire; Social Support for Exercise Survey; and other surveys assessing sleep, perceptions and intentions related to exercise, and PA change strategies used in previous behavioral health research. Psychological measures include the Rosenberg Self-Esteem Scale, Center for Epidemiological Studies Depression Scale, Spielberger State-Trait Anxiety Inventory, and Quality of Well-Being Scale. Other related lifestyle factors are measured using the Social Determinants of Health Toolkit, RAND Homelessness Survey, and Customary Drinking and Drug Use Record. Participant experience and satisfaction is measured using the Twente Engagement With eHealth Technologies Scale and the User Burden Scale.

Continuous measures include PA, intervention engagement, and SCT constructs and key process variables. PA is measured as steps per day and minutes of MVPA through the Fitbit Versa smartwatch. Quantitative markers of engagement for all participants include use of the Fitbit smartwatch and smartphone app and progress toward daily step goals and accompanying accrual of points. Additional markers of engagement for participants receiving the YourMove intervention include adherence in responding to daily EMAs. Participant responses to daily EMAs enable measurement of SCT constructs for our dynamic SCT model, described in the YourMove Intervention section, and key process variables. Key SCT constructs and process variables include (1) behavioral outcomes (ie, sleep, mood, physical fitness, and physical appearance), (2) busyness, (3) stress, (4) typicalness of the day, (5) internalized cue to action, (6) commitment to goal, (7) self-efficacy for meeting the daily goal, and (8) outcome expectancies (ie, sleep, physical appearance, mood, concentration, and physical fitness). The timeline for outcome measurement are shown in Figure 7.

**Figure 7 figure7:**
[figure not shown]
A timeline for outcome measurement. *Primary outcome measure; EMA: ecological momentary assessment; MVPA: moderate to vigorous physical activity; SCT: social cognitive theory.

#### Fitbit Versa Smartwatch and Smartphone App

All participants receive a consumer-level Fitbit Versa smartwatch and corresponding smartphone app. The Fitbit Versa is a wrist-worn device that objectively measures PA through its triaxial accelerometer, optical heart rate monitor, and altimeter. Upon syncing the device, participants can view PA measurements, including steps and MVPA, on the Fitbit smartphone app. Data collected from the Fitbit smartwatch are passively and securely streamed to the Fitbit website. They are then retrieved using Fitabase [78], a web-based application developed by Small Step Labs LLC. This allows for the simultaneous collection of high-resolution Fitbit data from large numbers of participants and integration with the COT approach controller and SMS text messaging system. Fitbit was chosen as the digital technology tool as it was deemed the most viable technology platform that balanced the various constraints of the study with respect to privacy, access and usability, data management, and risks and benefits. The digital health checklist mentioned previously was used to guide decision-making specific to our wearable device selection.

#### Financial Incentives for Meeting Daily Step Goals

On the basis of a review of worksite wellness programs and the literature [79-81], we found that it is plausible to assume that worksite wellness offerings will provide both wearable devices to employees and financial incentives for meeting health targets. On the basis of a review of options (coupled also with our design work described previously), we determined that US $50 in financial incentives for meeting step goals was a fiscally viable target that could be scaled and implemented at scale within worksite wellness offerings. On the basis of this, participants in both the YourMove intervention and active control are eligible to receive up to US $50 for meeting their suggested step goals. In both groups, 1000 points translate to US $1, but the approach for establishing the daily suggested step goal and number of available points varies across the 2 groups, described in detail in the following sections.

#### Tailored Text Messaging Support for Exercising

All participants receive a weekly exercise goal and feedback, behavior change strategies, and reminders to wear the Fitbit Versa smartwatch via the Fitabase SMS text messaging system. In total, 3 to 4 SMS text messages are delivered each week and follow a consistent weekly schedule, shown in Multimedia Appendix 8. Each week, participants are encouraged to achieve 150 minutes of MVPA. While this static goal is not adjusted dynamically as with the controller-generated daily step goals, participants receive personalized, tailored feedback on progress toward reaching the goal based on data collected from the Fitbit Versa smartwatch. In addition, in instances in which a participant exceeds the goal, tailored feedback encourages achieving 300 minutes of MVPA, which is associated with additional health benefits [63-65]. The behavior change strategies focus on physiological characteristics, behavioral drive, motivation, opportunity, and resiliency conditioning. Finally, if no data have been collected from the smartwatch, participants are reminded to wear their watch in lieu of weekly midweek and end-of-week feedback.

### YourMove Intervention

#### Overview

For the week following randomization, participants are instructed to engage in their normal level of PA to establish a baseline measured by wearing the ActiGraph activity monitor and Fitbit smartwatch. During this time, participants do not receive any intervention components. Afterward, participants assigned to the YourMove intervention group receive (1) the Fitbit Versa and corresponding smartphone app, (2) daily personalized step goals with corresponding point rewards generated using our COT approach, (3) the weekly PA goal (150 minutes of MVPA per week) with accompanying motivational and informative content via SMS text messaging, and (4) the Reflect tool delivered via Qualtrics. Each of these components is discussed in detail in the subsequent sections.

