### Study Design

The YourMove study is an RCT with a sample of 386 inactive adults aged 25 to 80 years. Participants are randomized to either the YourMove intervention or active control group. The primary outcome is change in minutes per week of MVPA at 12 months relative to baseline as measured via the ActiGraph activity monitor [49-51] using standard procedures [53,54]. Assessments of these constructs are conducted through a combination of in-person measurement at the Exercise and Physical Activity Resource Center (EPARC) at the University of California, San Diego (UCSD), and continuously via the Fitbit smartphone app and wearable PA monitor.

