##### Phase 1: Baseline

The purpose of this phase is to obtain an estimate of a person’s median steps per day before receiving any active intervention save for the Fitbit Versa itself. To do this, participants are asked to wear the Fitbit smartwatch for 10 days but otherwise do not receive any other type of support. Participants are also asked to engage in their normal PA activities to the best of their abilities. Neither suggested daily goals nor points are provided to participants during this phase.

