Step goals are minimally personalized in that they are all calculated in reference to a person’s median steps per day. Thus, for example, in the first cycle of the system ID experiment, the 10 days of the baseline phase are used to calculate the median steps per day as the reference for defining the lower range of a person’s suggested steps per day goal. Points are not personalized in this phase (eg, a person receives suggested points each day ranging from 0 to 500 points).

Pseudorandom input signals are used to dynamically and experimentally vary suggested step goals and points. Within a system ID experiment, a key concept is the notion of a cycle. A cycle is used to define the length of time needed coupled with other constraints (discussed in the following section related to input signal design) to ensure sufficient excitation of variance at a sufficient length of time to generate a computational model of the dynamic system for each individual. For this, key considerations include designing an input signal within a given cycle to have confidence that enough variations (some days with high goals, some with low suggested goals, and some with intermediate goals and, similarly, some days with a high number of points, an intermediate number of points, or no points) exist to create an estimate of the influence of steps goals and points for each person over time and across variations in context. In addition, a cycle needs to be long enough to ensure that the 2 intervention input signals are orthogonal to one another and not aligned with any known temporal patterns (eg, they do not align with a 7-day weekly cycle, which would make it impossible to disambiguate the influence of the intervention option relative to the impact of day of the week).

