### Active Control

In addition to all the common elements described in the previous sections (eg, Fitbit smartwatch, US $50 in incentives for meeting step goals, and tailored SMS text messaging support), participants assigned to the active control group, similarly to those assigned to the YourMove intervention group, are instructed to engage in their normal level of PA for 1 week to establish a baseline, shown in Figure 7. This is followed by the intervention phase, during which participants receive a daily step goal along with an accompanying number of points earned each day that they reach their goal. Unlike the YourMove intervention, the daily step goal and accompanying number of points is kept fixed (10,000 steps per day and 150 points per day, respectively). The goal is delivered to participants via the standard Fitbit app features, and points are communicated via email. Participants also receive a weekly PA goal and the same accompanying motivational and informative SMS text messages as those for the YourMove intervention group described previously. Finally, the active control condition does not include the self-guided self-experimentation tool (Reflect) featured in the YourMove intervention condition.

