### Statistical Analysis

#### Overview

For the comparison of a 12-month change in minutes per week of MVPA from baseline between the intervention and control groups, a 2-sided, 2-sample 2-tailed *t* test with a significance level of .05 (or a nonparametric approach such as the Wilcoxon rank sum test if parametric assumptions fail) will be conducted. In general, analyses will incorporate the intention-to-treat principle, which includes all participants who are randomized in the analysis. A mixed model for repeated measures (MMRM) will also be considered. The dependent variable in the MMRM is the change from baseline in minutes per week of MVPA at each postbaseline visit (6 and 12 months). Independent variables in the MMRM include study arm, visit (as a categorical variable), arm-by-visit interaction, minutes per week of MVPA at baseline, and potential covariates of interest (eg, baseline BMI, sex, age, ethnicity and race, marital status, parental status, employment status, and smoking status) that are determined a priori. Potential covariates significantly associated with outcome (*P*<.10) will be included in a multivariable logistic regression model. To avoid inflation of the type I error, we will use permutation tests for inference. Missing data will be evaluated. If the missingness is not random (nonignorable), multiple imputation or propensity weighting will be considered. There will be no planned interim analyses for efficacy or futility conducted for this study. In addition, a frequency table comparing the arms in terms of meeting the guidelines (dichotomized as *yes* or *no*) will be created, and a Fisher exact test will be conducted. Furthermore, a generalized estimating equations regression will be conducted with meeting the guidelines (*yes* or *no*) as the dependent variable and visit, arm, and visit by arm as interaction terms in the model using an appropriate correlation structure adjusted by similar covariates to those of the primary aim. Statistical analyses will be conducted using the statistical software R (version 4.1.2).

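### The article places the ActiGraph baseline week after randomization, so any arm difference in that week's activity would pass in full into the change-score primary analysis

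*Protocol article*

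**What the plan says.** The Study Design section defines the endpoint: "The primary outcome is change in minutes per week of MVPA at 12 months relative to baseline as measured via the ActiGraph activity monitor". The Statistical Analysis section tests the 12-month change between arms with "a 2-sided, 2-sample 2-tailed *t* test with a significance level of .05", or a rank test if parametric assumptions fail. An MMRM with baseline MVPA as a covariate is mentioned only as something to be considered.

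On timing, the Overview of the YourMove Intervention section says: "For the week following randomization, participants are instructed to engage in their normal level of PA to establish a baseline". It names the ActiGraph and the Fitbit as the devices worn and adds that no intervention components are given in that week. The Active Control section says that participants already assigned to control "are instructed to engage in their normal level of PA for 1 week to establish a baseline", without naming the device.

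The Recruitment, Enrollment, and Retention section says: "After eligibility, consent, and BMI were confirmed and baseline measurements were completed, participants were randomized". The Measurement Protocol sets ActiGraph wear at 7 days.

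**The concern.** A change score treats the subtracted value as a pre-treatment quantity, which randomization balances in expectation. If that value is collected after allocation, the guarantee holds only if the arms behave alike in that week. Participants who know their arm may not: enthusiasm in one arm, or disappointment in the other, could move a week of activity. Whatever differs between arms at baseline is subtracted from the 12-month comparison and appears as a treatment effect of the opposite sign.

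The article does not rule this out. Its trial-integrity section describes blinding for outcome staff, the principal investigator and the statistician, not for participants. Candidates are told before enrolling that they may be assigned to an active control. Study Limitations concedes that full blinding is hard to achieve.

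**Working it through.** **The article's own figures.** Inputs from Power Considerations: effect size 0.32, SD of change 94 min, difference 30 min/week, two-sided alpha .05, power 80%, attrition 20%.

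- 30 / 94 = 0.319, consistent with 0.32.
- n per arm = 2 × (1.960 + 0.842)² / 0.32² = 153.3, rounded up to 154.
- 154 / 0.80 = 192.5, rounded up to 193 per arm, or 386 in total. This matches the article, so the sample size is not in question.

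**Standard error of the primary contrast.** With 154 evaluable per arm, SE = 94 × √(2/154) = 10.7 min/week.

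**Effect of a differential baseline shift.** Let b be the absolute difference between arms in baseline-week MVPA caused by allocation. The change-score contrast moves by b: upward if YourMove is the lower arm at baseline, downward if it is the higher. The article gives no value for b, so the values below are assumptions. Under the normal approximation:

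- Type I error with no true effect = P(|Z + b/SE| > 1.96).
- Power with a true 30 min effect, when the shift works against YourMove = P(Z > 1.96 − (30 − b)/SE).

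| b (min/week) | Type I error | Expected estimate if true effect is 30 and YourMove is higher at baseline | Power |
|---|---|---|---|
| 0 | 5.0% | 30 | 80% |
| 5 | 7.5% | 25 | 65% |
| 10 | 15.4% | 20 | 46% |
| 15 | 28.8% | 15 | 29% |

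For b = 10, b/SE = 10/10.7 = 0.93. That shift is one third of the planned 30 min difference.

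**With baseline as a covariate.** Only the slope times b carries through. For b = 10 and assumed slopes of 0.3, 0.5 and 0.7, the bias is 3, 5 and 7 min. Suppose the baseline and month-12 SDs are equal and the slope is 0.5. The SD of change, 94, then equals the SD at each visit, and the adjusted SE is 10.7 × √(1 − 0.5²) = 9.3. The bias ratio is 5/9.3 = 0.54, giving a type I error of about 8.4% instead of 15.4%.

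**The timing statements side by side.** Seven days of wear cannot be completed at a single visit. The recruitment text and the YourMove Overview are therefore compatible only if baseline measurements in the former means the clinic-visit measures. That reading removes the conflict in wording but leaves the ActiGraph week after allocation.

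**The case against.** The strongest reply is that nothing shows the arms differed in that week. Bias needs participants to know their arm before or during the wear week, and the article does not say when they are told. No intervention components are given then, and reactivity to wearing a Fitbit applies to both arms and cancels. This stands: the calculation shows sensitivity, not an estimate of actual bias. The timing also rests mainly on one loosely drafted paragraph, which has the Fitbit worn during the week and also received afterwards. Figure 7, the measurement timeline, was not visible here and may settle the order.

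Four stronger readings are tempting and not supported:

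- **That several places put the ActiGraph week after allocation.** The statement "At the baseline measurement visit, after enrollment and randomization, participants received a Fitbit Versa" concerns the Fitbit only.
- **That the baseline lengths conflict.** The COT section says "participants are asked to wear the Fitbit smartwatch for 10 days but otherwise do not receive any other type of support", and that "the 10 days of the baseline phase are used to calculate the median steps per day as the reference". This is a Fitbit phase for setting step goals, and a 7-day ActiGraph week can sit inside it.
- **That YourMove participants had a reason to hold baseline activity down to obtain easier goals.** The article does not say they are told of the link. The initial baseline median is the reference only for the first cycle, and the input is Fitbit steps rather than ActiGraph MVPA. Extra enthusiasm in YourMove is as plausible and would bias towards no effect.
- **That participants without a valid baseline week drop out of the analysis.** The article invokes intention to treat and contemplates imputation or weighting.

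The MMRM would partly address the problem, but the article does not commit to it, and it too conditions on the post-allocation week.

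**Conclusion.** The point holds in a limited form. The article places the baseline of its primary outcome after randomization, and the visible text nowhere puts the ActiGraph week earlier or says participants are unaware of their arm. The raw change-score t test is the analysis most exposed to this, because it passes a differential shift through in full. At an assumed 10 min/week the consequence is a type I error of about 15%, or power of about 46%, depending on direction. At zero differential shift nothing changes. These figures assume 154 evaluable per arm and the article's SD of 94. The size and direction of any shift are unknown, and the route depends on participants knowing their arm. A reader might infer that the result will be biased in favour of YourMove, but the article does not support that.

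**What to change.** 1. Reconcile the recruitment section, the YourMove Intervention Overview and the Active Control section, and state the order of randomization, arm disclosure and ActiGraph wear.
2. Make the primary comparison 12-month MVPA with baseline MVPA as a covariate, in place of the raw change score. This reduces the carry-through but does not remove it.
3. Report baseline-week ActiGraph MVPA by arm with a confidence interval.
4. If disclosure preceded or overlapped the wear week, pre-specify a sensitivity analysis of 12-month MVPA adjusted only for pre-randomization measures: screening IPAQ, sex, age and BMI. Do not require it to agree with the primary analysis. Its power cannot be computed from the article, which gives no month-12 SD, and it leans on self-reported activity.

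Enrolment is complete, so the timing itself cannot change. The article reports that data analysis had not begun, so at that point the analysis could still be fixed in advance. The cost is clarified wording and one extra analysis on data already collected, less precise than the ActiGraph-adjusted model. For scale, under the equal-SD, slope 0.5 assumption, the SE before any covariate gain is 10.7 against 9.3.
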